#### Secondary

The secondary objectives relate to the secondary outcomes and include assessment of whether the 5-day course is: (1) non-inferior to the 10-day course with respect to either participant or caregiver absenteeism (from daycare/school or work, respectively); (2) associated with lower rates of mild drug adverse reactions, anaphylaxis, or other severe drug adverse reactions than the 10-day course; (3) associated with superior adherence to study medications than the 10-day course; (4) non-inferior to the 10-day course with respect to recurrence of respiratory illness within 30 days of cure; and (5) associated with lower rates of antibiotic-resistant organism (ARO) colonization and/or disruption of the gut microbiome than the 10-day course.

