### Inclusion criteria

Children aged 6 months to 10 years presenting with CAP will be eligible. Similar to other trials [16–19], CAP will be defined if all of the four following numeric criteria are met:Fever (>37.5 °C axillary, >37.7 °C oral, or >38 °C rectal temperature) recorded in the ED or at home in the 48 h prior to presentation.Any one ofTachypnoea on examination (>60 breaths per minute (bpm) at age <1 year, > 50 bpm at age 1–2 years, > 40 bpm at age 2–4 years, and > 30 bpm at age >4 years);Cough on examination or history of coughIncreased work of breathing on examination (characterized by the presence of scalene muscle use, or suprasternal recessions/in-drawing, or intercostal retractions, or subcostal recessions/in-drawing); orAuscultatory findings (focal crackles, bronchial breathing, etc.) consistent with pneumonia.Infiltrates on chest radiograph consistent with bacterial CAP as judged by the ED physician.The attending ED physician diagnoses the child with primary CAP (children treated with systemic steroids in the ED will be presumed to have primary asthma exacerbation with possible infection and therefore will not meet inclusion criteria).

To be included, participants must be well enough to be treated as outpatients (adequate volume status, able to tolerate oral medication, oxygen saturation >90%, no evidence of impending respiratory failure); if a child is ill enough to be admitted to hospital, it might be unwise to attempt short-course therapy. Additionally, eligible participants must have no evidence of empyema or necrotizing pneumonia, as routine management of these conditions would require parenteral antibacterial agents (and admission to hospital).

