#### Follow up

The RA will phone the caregiver once at day 3–5 and once at day 7–10 to verify the clinical stability of the participant. Caregivers will also be explicitly informed that they can contact the study team in the event of a concern prior to the scheduled phone calls. The caregiver will be given a study diary to complete each day, which will include the following: temperature, dyspnoea (older participants), increased work of breathing, school attendance, caregiver absenteeism from work duties, days of mild diarrhoea, mild (abdominal discomfort, rash) and severe (anaphylaxis) drug adverse reactions, and the number of missed medication doses, if applicable. The caregivers will be instructed how to take their child’s temperature and assess increased work of breathing. Any participant who has persistent fever more than 3 days post-enrolment will receive an additional 5 days of open-label amoxicillin after the initial 5 days (i.e. will receive a guaranteed 10 days of antimicrobial agents). Any participant who worsens clinically subsequent to enrolment at any time point prior to the primary outcome visit will be urged to seek medical care without delay either at the site where recruitment took place or with another physician (e.g. family physician, walk-in clinic); all participants will be provided with printed documentation about the SAFER trial and contact information for the local Principal Investigator (PI) for the benefit of the medical professional re-evaluating the participant. The criteria for permanent discontinuation of the experimental aspect of the study protocol in an individual subject are as follows: failure to defervesce by day 4 post-enrolment; requirement for hospitalization because of worsening respiratory illness; severe reaction potentially associated with amoxicillin, such as a generalized allergic reaction (urticarial rash, bronchospasm, angioedema, hypotension, etc.); requirement for prohibited concomitant medications; completion of treatment/intervention as defined by the protocol; or clinical reasons believed by the physician to be life-threatening.

The daily symptom diary will include prompts to aid caregivers to remember the three daily doses of study medication. The RAs will also encourage optimal adherence to medication administration at baseline and at each of the two scheduled follow-up phone communications.

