All serious AEs (SAEs) that are both unexpected and related to the study product will be reported to Health Canada, and those related to the study product or procedures will be reported to the appropriate REB as soon as possible if required by the REB, but no later than 15 calendar days (7 days if fatal or life-threatening) after first knowledge of the event. Further information and significant new information on ongoing reported SAEs will be provided to the sponsor, the REB and Health Canada, as applicable. Copies of all information about the SAE will be kept in the regulatory binder.

All caregivers will be asked to complete a symptom diary form each day post-randomization until the tenth post-randomization day; questions on this form will seek information on clinical features of persistent or worsening respiratory disease (e.g. fever, difficulty breathing, overall clinical status) in addition to common (e.g. diarrhoea) and serious (e.g. anaphylaxis) AEs known to be associated with amoxicillin administration. In addition, the RA will specifically ask about symptoms and signs consistent with respiratory deterioration or amoxicillin-associated AEs. This will also be done at the time of visit 1, when the participants return to be clinically evaluated at day 14–21 post-randomization.

The SAE most likely to occur is hospitalization in the first few days post-recruitment, due to worsening respiratory status. Though the majority of children with mild CAP respond well to oral antimicrobial therapy, a small percentage will worsen and require admission to hospital because of progressive oxygenation failure and/or the need for operative drainage of pleural-based collections. These SAEs would not be related to any trial procedures, as all study participants will be receiving the first-line antimicrobial agent of choice (high-dose amoxicillin) for the first 5 days post-enrolment. We note that the risk of harm to trial participants will likely be less than to non-participants, because study staff will be contacting all study participants at intervals to verify clinical stability. As detailed above, the RAs will contact all study participants once at day 3–5 post-recruitment and once at day 7–10 post-recruitment and will be actively questioned about symptoms indicative of worsening respiratory status. Furthermore, all participants that are persistently febrile at day 4 post-recruitment will complete 10 days of open-label high-dose amoxicillin.

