#### Analysis

We will use descriptive statistics to describe the baseline characteristics of the groups reported as count (percent) for categorical variables, and mean (standard deviation) or median (first quartile, third quartile) for continuous variables, depending on the distribution. We will adopt Consolidated Standards of Reporting Trials (CONSORT) criteria for reporting on non-inferiority and equivalence trials in reporting the trial [38]. The principal analysis will be per- protocol, as is recommended for non-inferiority trials [39–41]. The principal analysis is not intention-to-treat (ITT) simply because the effect of ITT analysis is to reduce the difference seen between treatment groups; in a superiority trial, ITT analysis functions to buttress a conclusion of superiority, but in a non-inferiority trial it could lead to a false conclusion of non-inferiority by masking a true difference between treatment arms.

We will use logistic regression to analyze binary outcomes, Poisson regression for count outcomes and linear regression for continuous outcomes. Descriptive analyses will be used to compare rates of viral and atypical co-infections in the entire study population and between groups.

We will perform some subgroup analyses by adding an interaction term between treatment group (5-day vs. 10-day course) and the following subgroups: (1) older (age 5–10 years) vs. younger (age <5 years); (2) higher vs. lower salivary CRP; and (3) virus/*Mycoplasma* detected in baseline NPS vs. no virus detected. These interaction tests will be exploratory in nature and not adjusted for multiple testing [42].

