These analyses will be exploratory. The following sensitivity analyses are planned: (1) intention-to-treat analysis; (2) strict per-protocol analysis including only those participants who were adherent to their medications and whose radiographs were reported by a radiologist to demonstrate alveolar infiltrates; (3) per-protocol analysis stratified by whether the saliva CRP was greater than the 75th percentile; and (4) per-protocol analysis stratified by whether a virus, an atypical pathogen, or high-level *S. pneumoniae* colonization was found in the NPS. If evidence is found of effect modification or confounding related to the above parameters additional analyses will be undertaken. The results of all analyses will be reported as estimate of effect, corresponding 95% CI and associated *p* values. All *p* values will be reported to three decimal places with those less than 0.001 reported as *p* < 0.001. The criterion for statistical significance will be set at alpha = 0.05. Table 1 provides a summary of the outcomes, corresponding hypotheses, measure, and method of analysis.

**Table 1 Tab1:** Variables, measures, and methods of analysis

Variable/outcome	Hypothesis	Outcome measure	Methods of analysis
Primary			
Clinical cure (per-protocol)	Short-course (5-day) treatment with high-dose amoxicillin is non-inferior to long-course (10-day) treatment	At visit (day 14–21) composite of: 1. Defervesced on or before day 4 2. No more than 1 further fever spike until visit 3. No tachypnoea and decreased work of breathing 4. No additional antibacterials given Dichotomous	Logistic regression
Secondary, between-group comparisons			
Absenteeism (caregiver, from work)	Short-course treatment is non-inferior to long-course treatment	Daily symptom diaries: self-reported number of caregiver-days absent from work (count)	Poisson regression
Absenteeism (child, from daycare/school)	Short-course treatment is non-inferior to long-course treatment	Daily symptom diaries: reported number of child-days absent from daycare/school (count)	Poisson regression
Mild drug adverse reactions	Fewer in short-course arm than in long-course arm	Daily symptom diaries: Reported number of child-days with diarrhoea, rash, abdominal pain, yeast infection (count)	Poisson regression
Anaphylaxis and other severe drug adverse reactions	Fewer in short-course arm than in long-course arm^a^	Daily symptom diaries, SAE reports. Dichotomous	Descriptive statistics

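### Child and caregiver absenteeism are planned as raw day counts with no denominator of days due, which adds variance that a plain Poisson standard error ignores; the child outcome is also worded in two ways

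*Protocol article*

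**What the plan says.** - **Objective.** The secondary objectives ask whether the 5-day course is "non-inferior to the 10-day course with respect to either participant or caregiver absenteeism", and name daycare/school for the child and work for the caregiver.
- **Measures.** Table 1 gives the child outcome as "reported number of child-days absent from daycare/school (count" and the caregiver outcome as "self-reported number of caregiver-days absent from work (count". Both come from the daily symptom diary, and both carry a non-inferiority hypothesis.
- **Model.** The Analysis section plans "Poisson regression for count outcomes and linear regression for continuous outcomes". The method cell for both outcomes in Table 1 reads Poisson regression and nothing more.
- **Population and window.** "Children aged 6 months to 10 years presenting with CAP will be eligible". Under Safety and adverse events, caregivers are to "complete a symptom diary form each day post-randomization until the tenth post-randomization day".
- **Diary content.** The Follow up section lists "school attendance, caregiver absenteeism from work duties" among the diary items. It lists no item for whether the child or caregiver was due anywhere that day.
- **Wording.** The Secondary outcomes list and the Follow up section refer to school only; the secondary objective and Table 1 refer to daycare/school. For caregivers, the Secondary outcomes list counts days on which work was disrupted, while Table 1 counts days absent.

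**The concern.** An absence can be observed only on a day when the child was expected at daycare or school, or the caregiver at work. In this age range some children will attend nothing, some caregivers will have no work to miss, and weekends fall inside a 10-day diary. In a raw count, an infant who is always at home and a pupil who missed no day both score zero.

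Two things are at stake. First, these zeros spread the counts well beyond what a Poisson model allows, so precision is lost and a standard error taken from the Poisson likelihood is too small. For a non-inferiority hypothesis, an interval that is too narrow is the less safe error. Second, if the diary asks about school alone, a toddler kept home from daycare may be recorded as having no absence. Analysis cannot repair that later, because the diary decides what data exist.

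**Working it through.** The article gives no number for absenteeism, so there is no figure of the plan's to reproduce. The check asks what non-attending children do to the estimate and to its standard error.

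**From the article:** 135 per arm (Sample size); a 10-day diary (Safety and adverse events).

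**Assumed, because the article gives no figures:** scheduled days are weekdays; each child's chance of missing a scheduled day follows Beta(1.2, 1.8), with mean 0.40 and variance 0.06, so E[P²] = 0.16 + 0.06 = 0.22; the share attending, s, is 80%, 60% or 40%.

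**Step 1, scheduled days W.** A 10-day window holds 8, 8, 8, 7, 6, 6 or 7 weekdays, depending on the start day. E[W] = 50/7 = 7.14 and E[W²] = 362/7 = 51.7.

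**Step 2, the ratio.** Mean absences per randomised child are s × 7.14 × 0.40. The factor s appears in both arms and cancels, so the ratio of means does not depend on attendance. Simulation with an absence multiplier of 1.25 gave a mean log ratio of 0.21 at every share, with or without an offset.

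**Step 3, true spread of the log ratio** (same absence distribution in both arms). Per attender, the mean is 7.14 × 0.40 = 2.86, and the mean square is 7.14 × (0.40 − 0.22) + 51.7 × 0.22 = 12.66.

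- Raw count, all children: variance = (2/135) × [12.66/(s × 2.86²) − 1]. At s = 0.6 this is (2/135) × 1.585 = 0.0235, so SD = 0.153.
- Offset, attenders only (135 × 0.6 = 81 per arm): the residual mean square is 7.14 × 0.18 + 51.7 × 0.06 = 4.39. The variance is (2/81) × 4.39/2.86² = 0.0133, so SD = 0.115.

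**Step 4, the plain Poisson standard error.** This is √(1/D₀ + 1/D₁), where D is the total number of absences per arm. At s = 0.6, D = 135 × 0.6 × 2.86 = 231, giving √(2/231) = 0.093. Non-attenders contribute no absences, so the figure is the same with or without the offset. It does not register the extra spread.

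| Attending | SD, raw count | SD, offset | Plain Poisson SE |
|---|---|---|---|
| 80% | 0.118 | 0.100 | 0.081 |
| 60% | 0.153 | 0.115 | 0.093 |
| 40% | 0.206 | 0.141 | 0.114 |

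**Step 5, simulation with the 1.25 multiplier.** At 60% attending: SD 0.152 raw and 0.110 with the offset, against a plain Poisson SE of 0.089. The raw count has (0.152/0.110)² = 1.9 times the variance.

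**Step 6, consequence if the plain SE were used.** When the true ratio sits exactly at a margin, the chance that the upper 97.5% limit falls below it is about Φ(−1.96 × 0.089/0.152) = 12.6% for the raw count and Φ(−1.96 × 0.089/0.110) = 5.6% with the offset (5.7% in simulation). The nominal value is 2.5%. The offset removes the part due to non-attenders. The rest is ordinary between-child variation, which needs a robust standard error.

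**The case against.** The strongest reply is that this is largely silence. The article calls Table 1 a summary, and an offset, an at-risk set or a robust standard error may be specified in a full protocol or analysis plan. That stands: the article does not exclude any of them. However, an offset needs days due to have been recorded, and the listed diary content does not mention them. The form itself is not shown.

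A second reply is that total days lost per randomised child is a legitimate measure of family burden in a pragmatic trial, and that a robust standard error alone would make its interval valid. Both points are correct. What remains is then lost precision, about 1.9 times the variance at 60% attending.

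A third is that school is merely shorthand. That is plausible, since the objective and Table 1 agree on daycare/school. It still needs settling where data are collected.

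A reader might go further and infer that the zeros pull the result towards non-inferiority. They would shrink an absolute difference: with an assumed 5.5 due days, 40% missed and a ratio of 1.3, the excess is 5.5 × 0.40 × 0.3 = 0.66 day per attender, but 0.6 × 0.66 = 0.40 day per randomised child at 60% attending. The article names no absolute-difference scale and no margin for absenteeism, and Poisson regression with its usual log link estimates a ratio, which Step 2 shows is not diluted. With a correct standard error the wider interval makes non-inferiority harder to show. Nor can a rate per diary day be called too low, because the article defines no such rate.

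**Conclusion.** The point holds as one of precision, standard errors and consistent definition, not as bias in the estimate. Table 1 sets both absenteeism outcomes as raw day counts with no days-due denominator, and the child outcome is worded differently in different sections. At an assumed 60% attending, the log ratio has an SD of about 0.15 for the raw count and 0.11 with an offset, while a plain Poisson standard error would report about 0.09. Across 40% to 80% attending the direction is the same and the size varies as tabulated. The sizes rest on assumed attendance and absence rates. The false non-inferiority figures further require that the plain standard error is used, which the article neither states nor rules out. Only secondary outcomes are affected; the primary conclusion on clinical cure is not.

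**What to change.** 1. Use daycare/school in the Secondary outcomes list and the diary description, to match the secondary objective and Table 1.
2. Have the diary record each day as not scheduled, attended or absent, for the child and for the caregiver's work.
3. In Table 1, fit the count model with offset log(scheduled diary days) among children with at least one scheduled day, and likewise for caregivers' work days, with robust (overdispersion-adjusted) standard errors.

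The cost is a few words in Table 1 and one more diary response option. The estimate then applies only to children and caregivers with scheduled days, which must be said when reporting. Recruitment has been open since August 2016 and about 60 pilot participants are rolled over. For those already followed, scheduled days may have to be approximated from existing attendance entries, and the approximation should be declared.

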### Study interventions

All study participants will begin the study receiving high-dose amoxicillin divided into three times daily and given orally for 5 days. Doses will vary over a range of 75–100 mg/kg/day within weight strata to simplify medication administration and reduce potential dosing errors. After the first 5 days of amoxicillin, half of the participants will take a second 5 days of amoxicillin dosed identically to the first 5 days (using a different product with a different flavour), and the other half of the participants will be given 5 days of placebo. This placebo will be Ora-Plus (NDC0574-0303-16) produced by Perrigo and distributed by Medisca, mixed with banana flavouring and sugar. No dose adjustments will be made.

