#### Secondary outcomes

Secondary outcomes will include:The number of days the participant is absent from schoolThe total number of caregiver days that their work is disrupted to care for the childThe number of days of mild drug adverse reactionsThe incidence of severe drug adverse reactions (including anaphylaxis)Participant adherence to the study medications, andRecurrence of respiratory illness after the primary outcome visit in the month after enrolment that leads to an ED visit or another antimicrobial course, andDevelopment of new antibiotic-resistant organism colonization and the degree of perturbation of the intestinal microbiome at day 14–21 post-enrolment and 3–6 months post-enrolmentDetermination of whether clinical cure rates are affected by baseline salivary C-reactive protein (CRP), baseline high-level *S. pneumoniae* nasopharyngeal colonization (>10 000 genome copies/mL), *M. pneumoniae* positivity, or NPS virus positivity

We feel that these outcomes are important to children and their caregivers, especially in mild illness with an excellent prognosis. These will mostly be participant-report or caregiver-report measures, and will be measured through participant documentation in the diaries; there will also be secondary verification by the research assistant (RA) at telephone contact on days 3–5 and 7–10 after enrolment. Microbiology outcomes will be measured through intestinal sampling at baseline, 14–21 days post-enrolment, and 3–6 months post-enrolment (see below).

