Adherence to study medications	Better in short-course arm than in long-course arm	Daily symptom diaries, RA interview: “adherence” defined as > 80% amoxicillin doses given (<3 doses of initial 15 doses in short-course arm, < 6 doses in reference arm) Dichotomous	Logistic regression
Recurrence of respiratory illness after primary outcome visit but before 30-day follow up	Short-course treatment is non-inferior to long-course treatment	RA interview. Dichotomous	Logistic regression
Development of antibiotic-resistant organism (ARO) colonization	Less frequent in short-course arm than in long-course arm	Enteric swab testing: “new colonization”’ defined as 3–6 month swab ARO positivity in context of baseline swab ARO negativity. Dichotomous	Logistic regression
Disruption of gut microbiome	Less marked in short-course arm than in long-course arm	Enteric swab testing: comparison of gut microbiome at 3–6 months to baseline gut microbiome. Continuous	Linear regression
Tertiary, entire-cohort			
Distribution of salivary C-reactive protein in cohort	Mean will be greater than that observed in children with bronchiolitis but less than that observed in children with empyema	Salivary swab testing: continuous	Descriptive statistics expressed as mean (95% CI)
Prevalence of high-level *S. pneumoniae* nasopharyngeal colonization	Majority of cohort will be positive	Nasopharnygeal swab (NPS) testing: Dichotomous	Percentage, with 95% CI
Prevalence of *Mycoplasma* detection	Minority of cohort will be positive	NPS testing: Dichotomous	Percentage, with 95% CI
Subgroup analyses			
Older (age 5–10 years) vs. younger (age <5 years)	Older age group will have higher salivary CRP values, lower rates of *S. pneumoniae* high-level colonization, more *Mycoplasma* positivity, and decreased rates of clinical cure	Clinical cure (as defined above)	Logistic regression with an interaction term between subgroup and treatment variables
Higher vs. lower salivary CRP	Higher salivary CRP will be associated with decreased rates of clinical cure	Clinical cure	Logistic regression with an interaction term between subgroup and treatment variables
Virus/*Mycoplasma* detected in baseline NPS vs. no virus detected (for primary outcome)	Detection of a virus or *Mycoplasma* will not affect observed rates of clinical cure	Clinical cure	Logistic regression with an interaction term between subgroup and treatment variables
Sensitivity analyses – for primary outcome only			

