Intention-to-treat	Results will remain robust	Clinical cure	Logistic regression
Strict per-protocol (those with adherence >80% and radiologist-verified pneumonia)	Results will remain robust	Clinical cure	Logistic regression

*SAE* serious adverse event, *RA* Research Assistant, *ARO* antibiotic-resistant organism, *CRP* C-reactive protein

^a^Too few events expected to be able to observe differences in treatment arms

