
The selection of the non-inferiority margin has a significant impact on trial outcome. It is clear that clinical considerations should inform the determination of the margin; if the margin is judged as unacceptably wide to clinicians, a “positive” non-inferiority trial will have little impact on practice. However, selection of the margin based solely on the clinical experience of the principal investigator should probably be avoided, despite how common this has been in the past. The US Food and Drug Administration (FDA) has provided guidance relating to statistical considerations affecting the selection of the non-inferiority margin [39]; note that their main concern seems to be that if the experimental treatment is found to be non-inferior to the standard therapy, there is sufficient evidence to be reasonably confident the experimental treatment is also superior to placebo [39]. The FDA draft guideline first instructs investigators to review meta-analyses of clinical trials of the standard therapy compared to placebo to discern the pooled estimate of efficacy; if only single trials are available, they can be used, but there will be much lower precision in the estimates of efficacy. Unfortunately, we cannot follow this guidance for the statistical determination of an appropriate margin for a trial such as SAFER because we do not have reliable data about the failure rate of placebo treatment of bacterial pneumonia in children living in the modern era. Estimates of child CAP-specific mortality from the pre-antibiotic era cannot be used since this would without doubt overestimate CAP-specific mortality in children today.

Adherence to medication is, in general, difficult to ensure. Caregivers of participants in this trial will be reminded far more frequently of the need to administer medication (via RA reminders and study diaries) than they would otherwise be; our adherence measures are similar to those in other major recent RCTs comparing short-course and standard-course antimicrobial therapy in children [56]. Despite this, it is entirely possible that adherence will be suboptimal, which could also predispose to a false conclusion of non-inferiority, especially if adherence to medication drops off after 5 days. From a practical standpoint, this is still important information for clinicians managing real patients, and would not greatly affect the generalizability of the results of the study (Additional file 1).

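### Adherence is scored over 15 doses in the 5-day arm and 30 in the 10-day arm, so the between-arm adherence test partly measures window length, and the strict per-protocol set probably filters the arms unequally

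*Protocol article*

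**What the plan says.** Study interventions: all children receive "high-dose amoxicillin divided into three times daily and given orally for 5 days". After that, "half of the participants will take a second 5 days of amoxicillin dosed identically to the first 5 days", and "the other half of the participants will be given 5 days of placebo". Screening, enrolment, and randomization leaves only the pharmacist aware of the allocation. Follow up describes diary prompts for three daily doses of study medication.

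Secondary outcomes names the outcome as "Participant adherence to the study medications". Table 1 (under Analysis) defines it as more than 80% of amoxicillin doses given, with the limits "<3 doses of initial 15 doses in short-course arm, < 6 doses in reference arm". The limits make sense only as doses missed. The hypothesis is "Better in short-course arm than in long-course arm", tested by logistic regression.

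The sensitivity analyses in the same table include "Strict per-protocol (those with adherence >80% and radiologist-verified pneumonia". The Analysis text describes this set as children who adhered to their medications. The Discussion concedes that adherence may be poor, "especially if adherence to medication drops off after 5 days".

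**The concern.** Days 1-5 are the same treatment in both arms, and on days 6-10 the family does not know which product it is giving. The 5-day arm is nevertheless scored only on the first bottle, and the reference arm on both. Two families with the same diary can therefore receive different labels because of the arm alone.

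Two results are at stake:

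- **The superiority test of adherence.** A difference may reflect the length of the scoring window and not what families did. The late drop-off that the Discussion anticipates is the pattern that can push the result towards the hypothesis.
- **The strict per-protocol analysis of clinical cure.** If it uses this variable, a child who takes the first bottle and abandons the second stays in the set in the 5-day arm and leaves it in the 10-day arm. Stopping late may be related to being well, being unwell or having a reaction, so this selection is not neutral.

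**Working it through.** **Reproducing the plan's limits.** Three doses a day for 5 days is 15 doses, and for 10 days 30.

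- 5-day arm: 1 - 3/15 = 0.80, so fewer than 3 missed is more than 80% of 15.
- Reference arm: 1 - 6/30 = 0.80, so fewer than 6 missed is more than 80% of 30. Over 15 doses the same limit would mean 1 - 6/15 = 0.60.

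Each limit agrees with 80% of that arm's own amoxicillin. There is no arithmetic error; the denominators differ. The 30 is not printed for the reference arm but follows from the dosing schedule and the limit.

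**Inputs.** From the article: 135 per arm (Sample size) and two-sided alpha 0.05 (Analysis). Assumed, because the article gives no miss rates: the share of doses missed, and its variation between children.

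**Model.** Behaviour is identical in both arms. Each child has logit(miss rate) = m + u, with u normal, SD 1.0, and the same u in both 5-day blocks. The value m is set so that the mean miss rate over children equals the stated figure. The two rules are:

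- 5-day rule: A = P(X1 ≤ 2), with X1 binomial(15, p1).
- 10-day rule: B = P(X1 + X2 ≤ 5) = sum over k = 0 to 5 of P(X1 = k) × P(X2 ≤ 5 - k), with X2 binomial(15, p2).

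Both are averaged over u.

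| Mean miss rate, days 1-5 then 6-10 | 5-day rule (A) | 10-day rule (B) | A - B, points | Chance of p < 0.05 |
|---|---|---|---|---|
| 5% then 5% | 92.6% | 95.5% | -2.9 | about 17% |
| 5% then 10% | 92.6% | 90.0% | +2.6 | about 12% |
| 5% then 15% | 92.6% | 83.5% | +9.1 | about 64% |

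Last column, third row: pooled proportion (0.926 + 0.835)/2 = 0.880. Null SE = √(2 × 0.880 × 0.120/135) = 0.0395. SE under the difference = √((0.926 × 0.074 + 0.835 × 0.165)/135) = 0.0391. Then Φ((0.091 - 1.96 × 0.0395)/0.0391) = Φ(0.35), about 0.64. The odds ratio is (0.926/0.074)/(0.835/0.165), about 2.5, with no difference in behaviour.

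**Strict set, third row.** The adherence filter alone removes 100 - 92.6 = 7.4% of the 5-day arm and 100 - 83.5 = 16.5% of the 10-day arm.

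**Range under other assumptions.**

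- SD 1.5, same means: 91.2% against 93.3%, 87.9% and 82.0% for the three rows; the chance of significance in the last is about 60%.
- Doses missed independently, no child effect: constant 5% gives 96.4% against 99.7%; 5% then 20% gives 96.4% against 84.1% (about 93% chance of significance).
- 10% of families stop after day 5, with independent 5% missing otherwise: 96.4% against 0.90 × 99.7% = 89.7% (about 58%).
- Constant missing strongly clustered by child (beta-binomial): only 1 to 2 points.

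**With one denominator** the difference is zero by construction. With independent missing of 5% then 20%, both arms show 84.1% on 30 doses, or both show 96.4% on the first 15.

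**The case against.** The strongest defence is that Table 1 openly measures amoxicillin exposure. A 5-day-arm child who skipped placebo still received the whole assigned active course, and keeping that child in a strict per-protocol set is defensible. This stands as a reason to report exposure. It does not support a superiority test between arms of an outcome labelled adherence to study medications, because families in the 5-day arm are also asked to give 10 days of product. Nor can this design show that a shorter course is easier to complete.

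Several stronger readings are tempting, and the article does not support them:

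- *Adherence behaviour is the same in both arms by design.* Not so. Amoxicillin and placebo on days 6-10 differ in content and may differ in side effects or recrudescence, so stopping can differ. Follow up also gives persistently febrile children open-label amoxicillin after day 5. Identical behaviour is used above only to isolate the effect of the rule.
- *Any adherence finding will be an artefact in favour of the 5-day arm.* Without miss rates neither size nor sign is established, and with rare or strongly clustered missing the effect is small.
- *The rule alone breaks randomisation in the strict set.* Any set conditioned on adherence after randomisation does so. The arm-specific rule adds asymmetry to that.
- *The principal per-protocol result is compromised.* Nothing in the article ties that analysis to this definition. Even its use in the strict set is an inference from the shared 80% threshold, since the amoxicillin-only count is not repeated there.

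**Conclusion.** The point holds in limited form. The adherence rule depends on the arm although both arms are dispensed a regimen of the same length, so the superiority test cannot be read as a comparison of adherence. Under the assumed patterns with SD 1.0, the rule alone shifts the comparison by between about -3 and +9 points. The large figures need a marked drop in adherence after day 5, a pattern the Discussion names as possible but does not quantify. The reach is one secondary outcome and, if the 80% criterion is the same variable as it appears to be, one sensitivity analysis of the primary outcome. An intention-to-treat sensitivity analysis that does not use the rule is also planned. This should be corrected, but it does not threaten the primary conclusion.

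**What to change.** In Table 1, define adherence identically in both arms: more than 80% of the 30 dispensed doses, that is fewer than 6 missed, whether amoxicillin or placebo. Add the word missed to the limit. Use this definition for the between-arm comparison, and name it explicitly as the criterion for the strict per-protocol set. State how children moved to open-label amoxicillin are counted, in the same way for both arms. Report amoxicillin exposure for days 1-5 and days 6-10 by arm as description only, without a superiority hypothesis.

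The cost is wording. Diaries record missed doses and run to day 10, and returned bottles are measured at the day 14-21 visit, so no new data are needed. There is a small downside: a 5-day-arm child who took all the amoxicillin but skipped placebo leaves the strict set. That set still selects on behaviour after randomisation, so the change gains symmetry without restoring the randomised comparison.
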